#### Data management {19}

All self-rated data will be entered by the participant and stored at a secure server at Karolinska Institutet. Interview data will be entered by the study administrator interviewing the participant into the same technical platform as the self-rated data and stored on the secure server at Karolinska Institutet. This study will use the BASS platform from the eHealth Core Facility at Karolinska Institutet for data management. Double data entry is not possible on the BASS platform; rather, all data is time-stamped. Range check will be conducted. No other data quality processes will be used.

#### Confidentiality {27}

All data will be will be collected and stored according to Good Clinical Practice, on a secure digital platform provided by the eHealth Core Facility at Karolinska Institutet. The data will be made available to other researchers upon reasonable request.

#### Plans for collection, laboratory evaluation, and storage of biological specimens for genetic or molecular analysis in this trial/future use {33}

N/A. There will be no collection of biological specimens.

### Statistical methods

#### Statistical methods for primary and secondary outcomes {20a}

Main and interaction effects will be estimated based on all available measurement points using mixed models with the appropriate family function. Incremental cost-effectiveness ratios will be calculated where the main effect in spent clinician time of a factor is divided by the main effect in alcohol consumption. The uncertainty in data for incremental ratios will be handled using nonparametric bootstrapping. An optimization criterion with the best possible effect on alcohol consumption given a maximum of 1 h of clinician time per participant will also be explored in order to select an optimal combination of guidance.

#### Interim analyses {21b}

There will possibly be interim analyses for clinical psychology student master theses, but no decision to terminate the trial will be based on the results from any student thesis.

### Methods for additional analyses (e.g., subgroup analyses) {20b}

We will explore who gained from the intervention under different levels of added guidance with regard to gender, age, and severity of alcohol problems.

#### Methods in analysis to handle protocol non-adherence and any statistical methods to handle missing data {20c}

Analysis will be intention-to-treat, i.e., without consideration of non-adherence and with estimation of missing data. We intend to conduct random effects modeling or similar statistical analyses which uses all available data to estimate missing data, without the need for imputation.

#### Plans to give access to the full protocol, participant-level data, and statistical code {31c}

Non-identifiable participant-level data may be available on reasonable request to the principal investigator, author MK.

### Oversight and monitoring

#### Composition of the coordinating center and trial steering committee {5d}

The trial team coordinating the study, including the principal investigator, will meet weekly during phases of the trial with active participants. The larger project managing group, including clinical and statistical expertise, will meet every 3–6 months.

#### Composition of the data monitoring committee, its role and reporting structure {21a}

There will be no data monitoring committee, as there is a low risk of harm and mainly self-rated data. Data integrity is secured by it being submitted to the secure technical platform at Karolinska Institutet as described under the “Data management {19}” section.

#### Adverse event reporting and harms {22}

Any adverse effects of the intervention will be measured at weeks 4 and 8 (during and immediately after the intervention) using self-rated questions. Adverse events in behavioral interventions usually entail stress or anxiety related to initiating a behavior change. No regulatory bodies will be contacted.

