### Digital psychological self-care—a new delivery format

Digital psychological self-care (DPSC) is a new proposed delivery format wherein an essentially self-guided digital intervention is provided within the framework of a structured care process that includes an initial clinical assessment interview with a clinician and one or several follow-up interviews [13]. The efficacy of well-designed self-guided digital interventions in depression and anxiety has in some studies been shown to be comparable to digital interventions with therapist guidance [14, 15]. Crucial for the improvement, however, seems to be a clear clinical process that employs clinical assessments and follow-up interviews, some form of clinical monitoring during the treatment, automated written support, and a material of high quality designed for the user to easily be able to guide themselves through the intervention [14]. The concept of DPSC is presented in a 2023 paper by [name] and colleagues [16].

We recently conducted a small feasibility study (*n* = 36) on a basic version of DPSC for problematic alcohol use named ALVA [13]. We found not only that the intervention was safe and credible but also that it rendered a high degree of use. In terms of effects, participants reduced their alcohol consumption from 22.6 standard drinks preceding week before the digital intervention to 10.6 standard drinks after the intervention (Hedge’s g intra-group = 0.85) and 12.7 standard drinks at a 3-month follow-up (Hedge’s g intra group = 0.70). The clinicians in the study spent less than 1 h on average per participant, time which was mainly spent on the initial clinical assessment interview and the post-intervention interview [13]. There was also a follow-up interview in the feasibility study, but this was not an essential part of the DPSC concept.

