### Research questions

What are the main and interaction effects of the two guidance forms investigated (i.e., mid-treatment phone call, weekly written messages) on alcohol consumption, immediately after the intervention and up to 12 months after the intervention?Which combination of guidance forms is most efficient (i.e., renders the greatest effects on alcohol consumption per additional cost in the form of incremental resource consumption measured by clinician time), immediately after the intervention and up to 12 months after the intervention?Which (combination of) guidance form(s) gives the best effects on alcohol consumption given a set limit of 1 h of clinician time per participant, immediately after the intervention and up to 12 months after the intervention?

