#### Outcomes {12}

Measurements will be made at registration (screening), before (week 0), during (week 4), and after the 8-week intervention (primary end-point, week 8), as well as at a 3-month follow-up (FU3), 6-month follow-up (FU6), and lastly at a 12-month follow-up (FU12). Measurements will take place in the form of self-assessment surveys via the secure digital treatment platform and supplemented with interview data from telephone interviews at week 0, week 8, and FU6. If there are sufficient resources available, a telephone interview may also be done at FU12.

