### Secondary outcomes

Diagnostic criteria Alcohol Use Disorder [22]

Credibility/Expectancy Questionnaire [23]

Alcohol Use Disorders Identification Test [19]

Brunnsviken Brief Quality of Life Scale [24]

Penn Alcohol Craving Scale [25]

Patient Health Questionnaire 9 [26]

Generalized Anxiety Disorder 7 [27]

Readiness To Change Questionnaire—treatment version [28]

Self-rated questions about any adverse effects of the intervention

See Fig. 1 for time points for all outcomes.

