### Data collection and management

#### Plans for assessment and collection of outcomes {18a}

Self-rated assessments will be made at registration (screening), before (week 0), during (week 4), after the 8-week intervention (week 8), at a 3-month follow-up (FU3), 6-month follow-up (FU6), and lastly at a 12-month follow-up (FU12). Telephone interviews will be made by the study administrators at week 0, week 8, and FU6. If there are sufficient resources available, a telephone interview may also be done at FU12.

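### Adverse-effect questions are scheduled only at weeks 4 and 8, so little can be said about harms beside the 3-, 6- and 12-month results (minor)

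*Protocol article*

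**What the plan says.** The section Adverse event reporting and harms {22} fixes the schedule: adverse effects are to be "measured at weeks 4 and 8 (during and immediately after the intervention"), by self-rated questions. The Secondary outcomes list includes the same instrument ("Self-rated questions about any adverse effects of the intervention") and points to a figure for timing: "See Fig. 1 for time points for all outcomes". That figure was not available for this review.

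The time frame for effects is longer. Each of the three research questions is asked "immediately after the intervention and up to 12 months after the intervention". Outcomes {12} plans measurements during and after the intervention, "as well as at a 3-month follow-up (FU3), 6-month follow-up (FU6), and lastly at a 12-month follow-up (FU12"). Section {18a} adds interviews: "Telephone interviews will be made by the study administrators at week 0, week 8, and FU6", with a further one at 12 months if resources allow.

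On the decision itself, the Primary outcome section applies the optimization criteria to drinking at week 8. Trial design {8} and Statistical methods {20a} build those criteria from effect on alcohol consumption and clinician time.

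**The concern.** The period in which adverse effects are asked about is much shorter than the period over which the guidance forms are compared. The programme lasts 8 weeks, so weekly written guidance presumably ends at about the last adverse-effect measurement. If losing that support has an unwanted effect, it would differ between the levels of that factor and would appear only after the questions have stopped. The reason given in section {22}, that adverse events usually come from starting to change a behaviour, does not cover the time after support ends.

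At stake is the reporting of the follow-up results. A paper giving 12-month effects and efficiency by guidance form would have no adverse-effect responses from the same period to set beside them. Differences in mean weekly drinks would not fill that gap, because a mean can hide individuals who got worse.

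**Working it through.** **Design figure.** The only design figure in the protocol is the sample size of 259 for a main effect of d = 0.35. Assuming a two-sided 5% level and 80% power, which section {14} does not state, power is 79.96% at N = 258 and 80.1% at N = 259. The figure reproduces, and nothing in it depends on the harms schedule.

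**Length of the two windows.**
- Intervention: 8 weeks (Intervention description {11a}). Last adverse-effect measurement: week 8 (section {22}).
- Last follow-up: 12 months after the intervention, following the wording of the research questions; taken as 52 weeks.
- Covered: 8 / (8 + 52) = 8/60 = 13%. Not covered: 52/60 = 87%.
- If the 12 months were instead counted from baseline: 8/52 = 15%. The reading makes little difference.
- As a share of the time in which the added guidance is delivered, coverage is essentially complete: the mid-treatment call falls inside the 8 weeks and the weekly messages run within them.

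**Which results are affected.**

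| Result | Time point | Adverse-effect questions at that time, per text |
|---|---|---|
| Primary outcome and optimization criteria applied to it | Week 8 | Yes |
| Effects and efficiency at follow-up | 3, 6 and 12 months | None stated |

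**Other measures.** PHQ-9, GAD-7, AUDIT, craving, quality of life and the diagnostic criteria for alcohol use disorder are secondary outcomes. They could show worsening after week 8 if Fig. 1 places them at follow-up. They do not ask about effects that the participant attributes to the intervention.

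**Feasibility figures.** Mean weekly drinks fell from 22.6 to 10.6 and then stood at "12.7 standard drinks at a 3-month follow-up".
- Reduction by the end of the intervention: 22.6 − 10.6 = 12.0.
- Rise afterwards: 12.7 − 10.6 = 2.1, or 2.1/12.0 = 17.5% of the reduction.
- Still below the starting value by 22.6 − 12.7 = 9.9.

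These are within-group means from 36 participants who received the basic version without added guidance. The protocol gives no interval for the 2.1-drink rise.

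**The case against.** The strongest case on the other side is that the schedule is a reasoned choice. The protocol expects low risk, ties adverse events to the start of behaviour change, and measures them during and directly after delivery. Week-4 and week-8 responses stay available for any later decision, and other scales may run through follow-up. This largely stands: the schedule is neither an error nor a contradiction. It does not remove the gap, because an effect that begins after week 8 cannot appear in responses given by week 8.

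Three stronger readings are tempting, and the documents do not support them.
- *The choice of guidance would be made without harms data.* The criteria are applied to the primary outcome at week 8, when adverse effects are measured. They contain no harms term at any time, so later collection would not alter the decision rule.
- *The protocol claims long-term benefit or safety.* It asks about effects up to 12 months; it claims neither benefit nor safety there.
- *The feasibility rebound shows harm from withdrawing guidance.* No guidance had been added in that study, so none was withdrawn. A partial rise in mean drinks that stays well below the starting value is not an adverse-effect signal.

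Fig. 1 might list later adverse-effect items. If so, it would disagree with section {22}, and the text would need correcting to match.

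**Conclusion.** The point holds as a minor one. As the text stands, adverse-effect questions cover about 13% of the period over which the guidance forms are compared (15% if follow-up is counted from baseline). Adverse effects arising after week 8 would not be recorded by the only adverse-effect instrument that the text names. The week-8 optimization decision, the sample size and the planned effect estimates are unaffected. What is limited is any statement about harms beside the 3-, 6- and 12-month results.

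This rests on two assumptions: that Fig. 1 agrees with section {22}, and that weekly guidance ends with the 8-week programme. No size can be put on the harms that might be missed, because the documents give no rate for them.

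**What to change.** Repeat the same self-rated adverse-effect questions in the surveys already scheduled at 3, 6 and 12 months, and report the responses by factor beside the follow-up effects and efficiency results.

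Also report, by factor and time point, the number of participants whose weekly drinks exceed their own week-0 value, with the number who gave data as the denominator. This uses the drinks data that the 12-month research questions already require. Because the measure is a single week's drinking, some participants will exceed their starting value by ordinary variation. The count should therefore be read as a comparison between factor levels, not as an absolute rate of harm.

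If items cannot be added, state in section {22} that adverse effects are assessed for the delivery period only and that no harms conclusion will be drawn for follow-up.

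The cost is slightly longer follow-up surveys and one more table. Participants already past a visit will lack the items. Recruitment opened on 11 January 2023, so the earliest possible participant would finish 8 weeks on 8 March and reach the 3-month visit in early June, before the protocol version of 30 June 2023. With recruitment expected to run to the last quarter of 2024, most follow-up visits still lay ahead at that version.

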#### Frequency and plans for auditing trial conduct {23}

There will be no independent auditing of trial conduct.

#### Plans for communicating important protocol amendments to relevant parties (e.g., trial participants, ethical committees) {25}

Any significant changes to the protocol require the trial coordinators to seek permission from the Swedish Ethical Review Authority.

#### Dissemination plans {31a}

Dissemination of trial results will include conference presentations and journal publications. All journal publications will be made publicly available with open access.

## Discussion

The published feasibility study [13] showed the potential of digital psychological self-care being safe, credible, and preliminary moderately effective in reducing alcohol consumption. This promising result was despite the base intervention being provided without any additional guidance other than around 1 h of clinician time spent on phone interviews. The present study could help finding the optimal level and mode of guidance to be given with the digital self-care intervention. This may be an important step towards implementing scalable, yet effective, interventions for individuals with problematic alcohol use within existing health care services.

### Trial status

Version 1, June 30, 2023. Recruitment started on January 11, 2023, and is expected to end in Q4 2024.

## Abbreviations

DPSC: Digital psychological self-care
ALVA: A digital psychological self-care intervention for problematic alcohol use
RCT: Randomized controlled trial
CBT: Cognitive behavioral therapy
AUD: Alcohol use disorder
CEQ: Credibility/Expectancy Questionnaire
AUDIT: Alcohol Use Disorders Identification Test
BBQ: Brunnsviken Brief Quality of Life Scale
PACS: Penn Alcohol Craving Scale
PHQ-9: Patient Health Questionnaire 9
GAD-7: Generalized Anxiety Disorder 7
RTCQ: Readiness To Change Questionnaire—treatment version
BASS: Technical platform at the eHealth Core Facility at Karolinska Institutet
FU3: Three-month follow-up
FU6: Six-month follow-up
FU12: Twelve-month follow-up
